### Data management and monitoring

All the data collected in this cohort study will be reported in an electronic case report form and managed on a web-based platform (iCReaT; Korea National Institute of Health, Cheongju, Republic of Korea). CRCs will be trained in using this system before initiating data entry and will enter the data according to standardized data entry guidelines. The data management will be coordinated by the Korea Institute of Oriental Medicine. Initially, a monitoring agent will be dispatched to each institution once per week for the first month, followed by monthly visits to ensure a seamless research process.

### Statistical analysis

We will conduct various analyses within the cohort. The results of the participants’ demographic data, the questionnaire-based prevalence of age-related symptoms and KM-based phenotype, physical function, and other outcome variables will be summarized using descriptive summary measures. For continuous outcomes, both univariate and multivariate linear regression analyses will be employed, while logistic regression will be used for dichotomous outcomes. Specifically, group differences (between KM-based phenotypes or between rural and urban areas) will be analyzed using Student’s t test and analysis of variance. The relationships between KM-based phenotypes and physical and psychological health, as well as demographic variables, will be analyzed using multiple regression.

Additionally, missing data patterns will be examined, and appropriate methods for handling missing data, such as Last Observation Carried Forward (LOCF) or Multiple Imputation, will be applied. Mixture models will be utilized to identify subgroups of subjects based on their biological and psychological characteristics. To estimate the cumulative risk of outcomes, Kaplan‒Meier analysis will be employed. Adjustments for covariates will be made before the follow-up period, during which Cox proportional hazard models will be used to estimate the risk of experiencing any of the outcomes. In addition, prediction modeling will be attempted by incorporating new covariates under investigation. P values less than 0.05 will be considered to indicate statistical significance. All statistical analyses will be conducted using SAS® version 9.4.

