### Study sample

This study will be conducted with a target group of 1000 participants who are entering old age and who are recruited from Wonkwang University Korean Medicine Hospital, a medium-sized city, and Jangheung Integrative Medical Hospital, a rural area in South Korea. The objective is to investigate potential cohort losses due to yearly mortality and other factors, with a target panel retention rate exceeding 80%. Despite limitations in achieving perfect representativeness of the population, practical feasibility will be considered by selecting research participants based on the demographic distribution of the population aged 50–65 years in Iksan and Jangheung, Jeonbuk, as of 2023 [16,17]. Considering the budget for this cohort project and the target population of individuals entering old age at Iksan and Jangheung in 2023 (for a total of 82,498 individuals), the goal is to recruit approximately 1% of this target population while factoring in a panel dropout rate of 20%. Therefore, the aim is to register a total of 1,000 adult participants, encompassing both sexes.

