### Study procedures

After commencing the research, banners for participant recruitment will be displayed in local public health care institutions and health centers. Contact will be initiated with individuals who respond to the banners; their age will be verified and visit schedules will be coordinated. Participants will be asked to maintain fasting for eight hours before their scheduled institution visit and to bring photographs of any nutritional supplements or medications that they are currently taking.

At the first visit, a research nurse will provide an overall explanation of the study. Then, the specific tests scheduled for the day will be detailed using a worksheet, with the nurse providing thorough explanations and addressing any queries immediately. After completing the explanations, participants will sign the research consent form and the consent form for the use of human-derived materials.

A medical registration form will be provided only to participants who sign both forms. For fasting patients, blood tests will be conducted first, and a light snack will be provided for those who complete the blood draw. Subsequently, participants will complete the all surveys and examinations. The entire examination process will take approximately 1 hour and 30 minutes. Upon completion, participants will be provided with information regarding their next examination date. Recruitment began on August 16, 2023, at Wonkwang University Korean Medicine Hospital and on August 22, 2023, at Jangheung Integrative Medical Hospital. It is expected to be completed by December 31, 2025.

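### The rural-urban contrast is assigned to an unadjusted t test or ANOVA with one volunteer-recruited hospital per region, so differences in age-sex mix could be reported as regional, and region cannot be separated from site

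*Protocol article*

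**What the plan says.** **Named test.** The Statistical analysis section states that "group differences (between KM-based phenotypes or between rural and urban areas) will be analyzed using" a Student's t test or an ANOVA. No covariate is attached to this.

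**Regression, in general terms.** The sentence before it reads: "For continuous outcomes, both univariate and multivariate linear regression analyses will be employed", with logistic regression for dichotomous outcomes. It names neither an exposure nor a covariate.

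**Regression, assigned.** The sentence after it reads: "The relationships between KM-based phenotypes and physical and psychological health, as well as demographic variables, will be analyzed using multiple regression". Region is not mentioned.

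**Covariate adjustment.** The only explicit statement is "Adjustments for covariates will be made before the follow-up period, during which Cox proportional hazard models will be used". It concerns follow-up and the Cox models, and names no covariate.

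**Sites and recruitment.** Under Study sample, participants are "recruited from Wonkwang University Korean Medicine Hospital, a medium-sized city, and Jangheung Integrative Medical Hospital, a rural area in South Korea", that is, one hospital per region. The same section speaks of "selecting research participants based on the demographic distribution of the population" aged 50 to 65 in the two areas. Under Study procedures, "banners for participant recruitment will be displayed in local public health care institutions and health centers", and people who respond are contacted and scheduled. Neither section says that the two sites are to be alike in age and sex.

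**The concern.** Describing health profiles in rural and urban areas is part of the stated aim, and the Introduction uses regional differences to justify the study. Many of the listed outcomes, such as grip strength, bone density, hormones, pulmonary function and physical performance, can be expected to vary with age and sex. If the two volunteer samples differ in age or sex, an unadjusted test carries that difference straight into the regional contrast.

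Selecting by the local demographic distribution does not remove the risk. Even if each site mirrored its own area perfectly, the two areas could differ from each other in age and sex.

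There is a second, separate problem. With one hospital per region, anything that differs between the hospitals (examiners, how volunteers come forward, handling of measurements) takes the same value as region for every participant. Several measures depend on the examiner, for example goniometry, core endurance, spirometry and hearing. At stake is whether a published rural-urban difference reflects region, demographic mix or site.

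**Working it through.** **The plan's own figure.** The article gives no power, effect size or site split for the regional contrast, so there is nothing to reproduce for it. The overall target is roughly consistent with its stated basis: 1% of 82,498 is 825, and 1,000 × 0.8 = 800, or 0.97%. It does not bear on this point.

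**Inputs from the article.** Total 1,000; ages 50 to 65; significance level 0.05 (taken as two-sided); two hospitals, one per region.

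**Assumptions, because the article gives no values.** 500 per site, ages uniform within the range, no true regional effect, and the gaps, correlations and slopes shown below.

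**Age mix alone.**
- SD of 16 equally likely ages: √((16² − 1)/12) = 4.61 years.
- Bias in outcome SDs = (age gap / 4.61) × correlation. Standard error = √(2/500) = 0.0632.
- 2-year gap, correlation 0.3: bias = 0.130, z = 0.130/0.0632 = 2.06, chance of P<0.05 = 53.9%.
- 1-year gap, correlation 0.2: bias = 0.043, z = 0.69, chance = 10.5%.
- No gap: 5%.

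**The same 2-year, 0.3 case at other splits.**
- 800/200: standard error √(1/800 + 1/200) = 0.0791, z = 1.65, chance 37.7%.
- 850/150: standard error √(1/850 + 1/150) = 0.0886, z = 1.47, chance about 31%.

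**Sex mix alone** (500/500, a 10-point difference in the share of women, sex gap D in within-sex SDs). Bias = 0.10 × D / √(1 + D²/4).
- D = 0.5: bias 0.049, chance 12%.
- D = 1: bias 0.089, chance 29%.
- D = 2: bias 0.141, chance 61%.

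**Does adjustment help?** A simulation of 2,000 runs assumed 500/500, women 55% v 65%, about 1.5 years' difference in mean age, a sex effect of 1 SD, an age slope of 0.03 SD per year, and no regional or site effect. The unadjusted t test was significant in 52% of runs. Regression on site, age and sex was significant in 5%.

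**Does adjustment separate site from region?** No. A design matrix with an intercept, region and hospital has rank 2 for 3 columns, so the two effects are not separately estimable. With a pure site shift of 0.15 SD added to the same simulation, the adjusted model was significant in 64% of runs. The unadjusted test was significant in only 5% there, but by coincidence: the age-sex bias, about 0.10 + 1.5 × 0.03 = 0.145 SD in the opposite direction, almost cancelled the shift.

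**The case against.** **Adjusted regression is already planned.** A reader might infer that the plan rules out an adjusted regional analysis. It does not: the general sentence on multivariate linear and logistic regression is not limited to the KM phenotypes. This is also a condensed article, and covariate lists are commonly left to an analysis plan. That part of the objection stands. What remains is that the one sentence naming the rural-urban contrast assigns it specifically to an unadjusted test, and nothing links the planned regression to it.

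**The size is assumed.** A reader might infer that age-sex mix will show up as a false regional difference. The article gives no age gap, sex gap, correlation or site split, and with no imbalance and no site shift the error stays at 5%. A 2-year gap is 0.43 SD of age (2/4.61), which is sizeable within this range. Only *could be reported* is supported.

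**Recruitment is more than an age check.** A reader might take the banners to contradict the demographic selection. They need not: banners are a channel, selection can be applied to those who respond, and trained coordinators apply all the eligibility criteria. The narrower fact stands that no balance between the sites is stated.

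**A crude comparison is legitimate.** As a description of two samples, it is. It becomes a problem when its P value is read as an effect of region.

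**Common instruments, central data management and monitoring.** These may reduce differences between sites, but they do not make site and region distinguishable.

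**Limits are acknowledged.** The article concedes imperfect representativeness. That concerns generalisation to the population, not confounding between the two sites.

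**Conclusion.** The point holds as a weakness in how the regional contrast is specified. The named method is unadjusted, the regression already planned is not linked to region, and age-sex balance between the two volunteer samples is not stated. Under the assumptions shown (500 per site, no true effect), the chance of a spurious significant result runs from 5% with no imbalance, through about 10% for a modest age gap, to about 54% for a larger one. It is lower for the larger gap if the sites are unequal in size. These figures illustrate the risk and do not predict what will happen.

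The aliasing of hospital with region does not depend on those assumptions. It follows from having one hospital per region, given that participants attend the hospital of their own area; the article describes no other arrangement. It is a limit of the design and not a consequence of choosing a t test, so regression does not cure it.

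Two stronger readings should be left aside. One is that the equal-variance form of the t test is itself a material fault: that depends on an unequal site split and unequal variances, neither of which the article gives. The other is that the study will draw conclusions about rural and urban Korea as a whole: no such result has been reported.

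**What to change.** 1. State in the Statistical analysis section that the rural-urban contrast comes from the linear or logistic regression already planned, with outcome regressed on site and adjusted for at least age and sex. Both variables are already collected (Table 1).
2. Keep the t test or ANOVA as a descriptive, crude comparison, labelled as such.
3. Choose any further covariates with care. Education, for example, is one of the social factors under study, so adjusting for it may remove part of the difference of interest.
4. Word the result as a difference between Iksan-area and Jangheung-area participants, and state that region and site cannot be separated.

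The cost is a change of wording, slightly more analysis and a more modest claim. No new data are needed.

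### The t test and analysis of variance named for phenotype and rural-urban differences assume equal variances; with unequal groups and unequal spreads their error rate leaves 5%, and a larger cohort does not bring it back

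*Protocol article*

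**What the plan says.** In the protocol article, Methods, Statistical analysis, the comparisons concerned are "group differences (between KM-based phenotypes or between rural and urban areas"; they "will be analyzed using Student’s t test and analysis of variance". No unequal-variance form is named. The criterion is "P values less than 0.05 will be considered to indicate statistical significance". Continuous outcomes are also to be analysed by univariate and multivariate linear regression, with no mention of robust standard errors.

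On group sizes, the Study sample section says that "the aim is to register a total of 1,000 adult participants" and speaks of "selecting research participants based on the demographic distribution of the population aged 50–65 years in Iksan and Jangheung". It gives no number for each area. Phenotype group sizes are something the study will observe: the Statistical analysis section plans to summarise "the questionnaire-based prevalence of age-related symptoms and KM-based phenotype". No standard deviation is given for any variable.

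**The concern.** Student's t test and classical analysis of variance pool the within-group variances. The pooled variance is dominated by the larger group, whereas the sampling variance of the difference is dominated by the smaller group. If the two spreads differ, the standard error is therefore wrong by a factor that depends on the split and the SD ratio.

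If the smaller group is the more variable, the standard error is too small and false positives exceed 5%. If it is the less variable, the standard error is too large and real differences are more easily missed. The Discussion says that phase II interventions will be tailored to phenotypes defined in phase I, so the reliability of phenotype comparisons has some bearing on what follows.

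**Working it through.** **Inputs.** From the article: the tests named, the two kinds of comparison, significance at P < 0.05 and N = 1,000. Assumed, because the article does not give them: a two-sided test, a smaller group of 10% to 50% of the sample, and an SD ratio r (smaller group / larger group) of 0.9 to 1.1 as the mild range and 1/1.5 or 1.5 as the stronger case.

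**Formula.** Let p be the share of the smaller group and set the larger group's SD to 1. Apart from a common factor 1/N:

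- true variance of the difference: Vt = r²/p + 1/(1−p)
- variance that the pooled test uses: Vp = (p·r² + 1 − p)·(1/p + 1/(1−p))
- limiting two-sided error = 2·[1 − Φ(1.96·√(Vp/Vt))]

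N cancels in Vp/Vt, which is why a larger sample does not help.

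**The plan's own figure first.** With equal SDs (r = 1), Vp = Vt for every split and the error is 5.0%. With p = 0.5, Vt = 2r² + 2 and Vp = (0.5r² + 0.5)·4 = 2r² + 2, so the error is 5.0% at any SD ratio. The nominal level is right whenever either condition holds; it takes both inequalities together to disturb it.

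**Worked case, 20:80.**

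- r = 1.5: Vt = 2.25/0.2 + 1/0.8 = 12.5; Vp = 1.25 × 6.25 = 7.81; √(7.81/12.5) = 0.791; effective critical value 1.55; error 12.1%.
- r = 1/1.5: Vt = 3.47; Vp = 5.56; √(5.56/3.47) = 1.265; effective critical value 2.48; error 1.3%.

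**All scenarios.**

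| Split | r from 0.9 to 1.1 | r = 1/1.5 | r = 1.5 |
|---|---|---|---|
| 50:50 | 5.0% | 5.0% | 5.0% |
| 30:70 | 4.1% to 5.9% | 2.2% | 9.3% |
| 20:80 | 3.7% to 6.4% | 1.3% | 12.1% |
| 10:90 | 3.3% to 6.9% | 0.7% | 15.4% |

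**Check by simulation** (normal data, 100,000 replicates per cell). At 20:80 with r = 1.5 the pooled test's error was between 12.0% and 12.2% at N = 800, 1,000, 10,000 and 100,000. Welch's t test stayed between 4.8% and 5.2% in every cell, with SD ratios from 0.5 to 2.

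**More than two groups.** Five assumed groups of 400, 250, 150, 120 and 80, with SDs rising from 1 to 1.5 as the groups get smaller, gave 10.3% for classical analysis of variance. With the SDs reversed it was 2.4%; with the first pattern at ten times the sample it was 10.4%. Welch's analysis of variance gave 5.0% to 5.1% in these three cases.

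**Regression.** Ordinary least squares on a single group indicator is the pooled t test, so the planned univariate regressions share the problem unless the standard errors are robust.

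**Price of switching when variances are equal.** For an effect that Student's test detects with about 79.9% power, simulated Welch power was 79.8% at 300/700, 79.7% at 200/800 and 79.4% at 100/900.

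**The case against.** The strongest reply is that this is a condensed article. A single paragraph lists families of methods, and Student's t test may be loose shorthand. The choice of variance form, checks and fallbacks is commonly left to a fuller plan, which is not shown. What stands of this: the article does not exclude an unequal-variance version, and a fuller plan may already specify one. But the point concerns a test that is named, not a detail that is absent, and naming a more robust one costs nothing.

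The second reply is that the size is assumed. This stands in full. No passage gives a site split, phenotype frequencies or SDs, and with SDs within about 10% of each other the distortion is modest even at 10:90.

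Third, the work is exploratory, without a designated confirmatory comparison, and relationships between phenotypes and health are assigned to multiple regression. That also stands, and it limits the consequence.

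A reader might go further in three ways that the document does not support:

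- That this cohort's error rate is 12% or 15%. Those are scenario values, not estimates for this study.
- That the rural and urban groups are known to be badly unbalanced. The reference to the areas' demographic distribution allows imbalance but sets no ratio.
- That the hormone, laboratory and omics variables will be screened with these tests. The Statistical analysis section does not say which variables the t test and analysis of variance cover.

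**Conclusion.** The point holds in a conditional form. The named tests rely on equal variances, nothing in the article secures equal groups, and where both size and spread differ the error rate moves away from 5% in either direction whatever the sample size. Over the assumed splits from 30:70 to 10:90, the error ranges from 3.3% to 6.9% for SD ratios of 0.9 to 1.1, and from 0.7% to 15.4% when the SDs differ 1.5-fold. If the groups turn out near-equal in size (two-group case) or in spread, there is little or nothing to correct. It ranks as a worthwhile, cost-free improvement and not as an error that undermines the study.

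**What to change.** In Methods, Statistical analysis, replace Student's t test and classical analysis of variance with Welch's t test and Welch's analysis of variance for the phenotype and rural-urban comparisons. State that the matching linear regressions use heteroscedasticity-robust standard errors. If a fuller analysis plan already specifies these forms, aligning the wording is enough. Name the Welch forms outright: they hold the level whether or not the variances are equal, so no preliminary variance test is needed to choose between them.

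The cost is a change of wording. SAS 9.4 has all of these methods, and recruitment, visits and sample size are unaffected. The power given up under equal variances is about half a percentage point at 10:90 and less at more even splits.

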**Fig 1 pone.0316986.g001:**
[figure not shown]
Schedule of assessments and procedures for aging cohort (KoMAC) study. Screening: Initial assessment phase before baseline visit, including consent and eligibility checks. Visit 1 (Baseline): Baseline data collection, including demographic survey, physical measurements, health habits, and initial health assessments. Visit 2 (1-year follow-up ±  4 weeks): Follow-up assessments conducted 1 year after baseline to monitor health changes, excluding clinical lab tests. Visit 3 (2-year follow-up ±  4 weeks): Final follow-up assessments conducted 2 years after baseline, similar in scope to Visit 2.

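### LOCF is listed as a suitable missing-data method in a cohort followed to observe change with age; if used on longitudinal outcomes, it would shrink that change

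*Protocol article*

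**What the plan says.** The Statistical analysis section states that "missing data patterns will be examined, and appropriate methods for handling missing data" are to be used. Its two examples come later in the same sentence: "such as Last Observation Carried Forward (LOCF) or Multiple Imputation, will be applied". LOCF and multiple imputation appear side by side as examples. The article gives no rule for choosing between them and does not restrict LOCF to outcomes that stay stable with age.

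Three other parts of the article bear on this:

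- **Purpose and schedule.** The Fig 1 caption describes Visit 2 as "Follow-up assessments conducted 1 year after baseline to monitor health changes, excluding clinical lab tests"; Visit 3 follows at two years. The Study population section and Table 1 place blood tests at baseline and the final visit only, and most other measures at all three visits.
- **Expected loss.** The Study sample section sets the cohort size "while factoring in a panel dropout rate of 20" per cent, "with a target panel retention rate exceeding 80" per cent.
- **Comparisons.** The Statistical analysis section plans to compare rural with urban participants, and Korean-medicine phenotypes with one another, by t test and analysis of variance.

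**The concern.** LOCF rests on the assumption that nothing changes after the last attended visit. In people aged 50 to 65 who are followed to see how function, cognition, bone density and laboratory values move with age, that assumption contradicts the quantity under study. Every dropout is held at a younger value, so the estimated mean change is pulled toward zero.

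The second risk concerns the group comparisons. If one area or phenotype loses more participants, or loses them sooner, more of its members are frozen early and its average change shrinks more. Two groups that age identically can then appear to age differently. That would be read as a finding about region or phenotype, which is what the cohort was set up to study.

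**Working it through.** **Inputs from the article.** Planned dropout 20%; visits at 0, 1 and 2 years; blood tests at 0 and 2 years only; 1,000 participants.

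**Assumptions, because the article gives no figures.** The 20% is cumulative over two years. Mean change is linear, d per year and so 2d over two years. Dropout is unrelated to outcome. Dropout timing and its split between groups are varied.

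**The plan's own figure.** The 20% enters through the cohort size: "the goal is to recruit approximately 1% of this target population", "for a total of 82,498 individuals". 1% × 82,498 = 825. Allowing for 20% loss gives 825 / 0.80 = 1,031, or 825 × 1.20 = 990. In reverse, 1,000 × 0.80 = 800, and 800 / 82,498 = 0.97%. The 1,000 reproduces as a rounded number. This does not bear on LOCF beyond confirming 20% as the planning value.

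**Mean change under LOCF, annual measures.** Let q be total dropout and f the share of dropouts lost before Visit 2. Completers contribute 2d, those lost before Visit 2 contribute 0, and those lost between Visits 2 and 3 contribute d. Divided by the true 2d:

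ratio = (1 − q) + q(1 − f)/2

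For blood tests there is no intermediate value, so every dropout contributes 0 and ratio = 1 − q.

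| q | f = 0 | f = 0.5 | f = 1 | Blood tests |
|---|---|---|---|---|
| 10% | 0.95 | 0.925 | 0.90 | 0.90 |
| **20% (planned)** | **0.90** | **0.85** | **0.80** | **0.80** |
| 30% | 0.85 | 0.775 | 0.70 | 0.70 |

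**False group differences, by arithmetic.** Let both groups truly decline by 2d.

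- *Unequal retention.* Assume one group loses 10% and the other 30%, all before Visit 2. LOCF gives 0.9 × 2d = 1.8d and 0.7 × 2d = 1.4d. The false gap is 0.4d, or 20% of the true decline.
- *Equal retention, unequal timing.* Assume both lose 20%, one entirely after Visit 2 and the other entirely before. LOCF gives 0.90 × 2d = 1.8d and 0.80 × 2d = 1.6d. The false gap is 0.2d.

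**False-positive rate, by simulation.** 4,000 runs, 500 per group, two-sided 0.05, equal true decline of 0.5 SD over two years, SD of change 0.7, half of dropouts before Visit 2 (all assumed).

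| Dropout in the two groups | Annual measures | Blood tests |
|---|---|---|
| 20% / 20% | 0.05 | 0.05 |
| 15% / 25% | 0.15 | 0.22 |
| 10% / 30% | 0.43 | 0.68 |

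The size depends heavily on the assumed decline. With unequal dropout the rates run from 0.07 to 0.17 at a decline of 0.2 SD, and from 0.38 to 0.99 at 1.0 SD. Analysis of completers stayed between 0.044 and 0.059 throughout, but only because simulated dropout was unrelated to outcome. If sicker participants leave, completers are biased too.

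**The case against.** The strongest reply is that LOCF is not prescribed. The sentence offers examples, makes the choice follow from the observed pattern, and already names multiple imputation. This is a condensed article, and the choice by outcome, the missingness assumption and the sensitivity analyses commonly sit in the full protocol or SAP. All of that stands, and a reader who infers that this study will use LOCF goes beyond the text. The point survives because it concerns something stated: LOCF is presented as appropriate here. Examining missingness patterns cannot show that an unobserved value stayed unchanged.

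A second reply is that the article names no analysis of change from baseline. The Discussion calls Phase I, the part detailed in the paper, cross-sectional; the t tests are not said to be on change; and Kaplan-Meier and Cox analyses would ordinarily censor dropouts. This also stands and limits the point to longitudinal outcomes. At baseline there is no earlier value to carry forward.

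Four stronger readings are tempting but not supported:

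- *That Visit 2 laboratory values would be filled from baseline.* Those tests are not scheduled at Visit 2, so the values are not missing, and nothing says they would be imputed.
- *That LOCF would fill the Visit 3 values of participants who cannot reach two years before follow-up ends in December 2025.* The dates do sit badly together, but that is a separate timeline inconsistency. The article does not propose LOCF as its remedy.
- *That standard errors would be too small.* Filled values are treated as observed, but no such effect was quantified, and the simulation held the false-positive rate at about 0.05 when dropout was equal.
- *That false differences arise wherever retention differs.* Non-zero mean change is needed as well. The article reports no differential dropout, targets retention above 80% and describes measures to secure it.

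**Conclusion.** The point holds in a conditional form. The article lists as appropriate a method whose central assumption conflicts with the purpose of the follow-up visits. If LOCF is applied to longitudinal outcomes at the planned 20% dropout, it recovers about 80-90% of the true mean 2-year change for annual measures and 80% for blood tests. These figures assume linear change, dropout unrelated to outcome, and 20% as the cumulative loss; the 85% midpoint further assumes an even split of dropout between the two intervals.

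False differences between areas or phenotypes are possible, not established. They need non-zero mean change together with unequal retention or timing, and the 10% versus 30% split behind the 0.4d example is an assumption. The bias is toward no change in either direction: a measure that improves on retesting would have its improvement understated.

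This is a wording correction worth making, not a flaw that undermines the cohort.

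**What to change.** In the Statistical analysis section, delete LOCF for longitudinal outcomes and replace it with wording such as:

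*Longitudinal outcomes will be analysed by likelihood-based mixed models using all observed visits, or by multiple imputation that includes baseline and prior-visit values, age, sex and site, under a missing-at-random assumption. A delta-adjusted sensitivity analysis will examine worse change after dropout.*

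Multiple imputation is already named, and the SAS 9.4 software that the article specifies provides PROC MI, MIANALYZE and MIXED. The visit schedule, data collection and sample size do not change. The cost is slightly wider confidence intervals and a little more analysis work, chiefly for the sensitivity analysis.
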